#### Secondary Outcomes

Secondary outcomes for the ICU work packages include ICU mortality; in-hospital mortality; hospital length of stay (the number of days from the date of ICU admission to date of ICU discharge or death); mechanical ventilation duration (total duration of mechanical ventilation in days); and ventilator-free days, and alive at day 28. In all 4 work packages, we will evaluate the incidence of general systemic complications during the hospital stay as a secondary outcome, including myocardial infarction, deep venous thrombosis, pulmonary embolus, hyperglycemia, acute kidney injury, and sepsis. The definition of the various general systemic complications is shown in Table S1 in Multimedia Appendix 1.

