In WP1, WP2, and WP3, several statistical analysis approaches will be considered to determine the association between high-dose corticosteroids and outcome, and statistical analyses will depend on the structure of the available data. A multivariable logistic regression model will be used with high-dose corticosteroids as exposure and survival at day 28 as an outcome. Covariates used for adjustment will include age, gender, BMI, smoking status, prior administration of corticosteroids during admission, comorbidity, sequential organ failure assessment score, oxygen saturation, partial pressure of oxygen in arterial blood–fraction of inspiratory oxygen concentration ratio, C-reactive protein, procalcitonin, ferritin, interleukin 6, D-dimer, lactate dehydrogenase, platelet count, lymphopenia, and level of respiratory support. Covariates can be added or removed based on insights from the data set or from the literature. A model might be constructed in which patients are matched on a propensity score based on their probability to receive high-dose corticosteroid treatment. Propensity scores will be determined using a logistic regression model with high-dose corticosteroids as a dependent variable and determinants of high-dose corticosteroids as independent variables. After matching, survival and mortality at day 28 and other outcome parameters will be compared between matched groups using logistic regression. A Cox proportional hazards model might be performed to determine the effect of high-dose corticosteroids on time to death while taking into account the days of administration using time-dependent covariates. Other approaches involving censoring weights for differential loss to follow-up (eg, marginal structural models) or competing risks (eg, joint models) might be explored.

Furthermore, we will use clinical and biological data to perform latent class analysis to search for subphenotypes, which respond more favorably to corticosteroid treatment. This heterogeneity of treatment effect will be evaluated by including the latent class analysis-derived subphenotype, corticosteroid exposure, and an interaction term of the 2 as c-variate in the above-described survival models. Heterogeneity of treatment effect is considered to be present if the interaction term has a *P* value of <.05.

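### If the optional matched analysis is run, it assigns logistic regression to outcomes that include three ICU day counts, for which ordinary logistic regression needs an undefined yes/no split

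*Protocol article*

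**What the plan says.** The main analysis paragraph of Statistical Analysis covers three work packages and is tentative: "In WP1, WP2, and WP3, several statistical analysis approaches will be considered to determine the association between high-dose corticosteroids and outcome", with the choice said to depend on how the data are structured. Matching is one of the options: "A model might be constructed in which patients are matched on a propensity score based on their probability to receive high-dose corticosteroid treatment". Once that option is taken, the wording becomes firm: "After matching, survival and mortality at day 28 and other outcome parameters will be compared between matched groups using logistic regression".

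Secondary Outcomes lists, for the ICU work packages, a mixture of outcome types.
- **Binary:** "Secondary outcomes for the ICU work packages include ICU mortality; in-hospital mortality". The systemic complications, collected in all work packages, are binary too.
- **Counted in days, first:** the stay outcome, worded as "hospital length of stay (the number of days from the date of ICU admission to date of ICU discharge or death".
- **Counted in days, second:** the time on the ventilator, worded as "mechanical ventilation duration (total duration of mechanical ventilation in days".
- **Counted in days, third:** the time off the ventilator, worded as "ventilator-free days, and alive at day 28".

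Elsewhere in the analysis paragraph, the first logistic model is for day-28 survival and the Cox model is for time to death. Marginal structural and joint models (the latter for competing risks) may be explored, but they are not tied to any of the day counts.

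**The concern.** The article does name a model here, and that model does not suit part of the set it is assigned to. This is different from leaving the choice to an analysis plan.

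Taken at its word, the sentence turns three day counts into yes/no variables. Two things follow. The comparison discards the ordering of days within each side of the split. The result also depends on a cut-off that the article does not state.

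A second matter concerns the outcome definitions, whatever model is used. Length of stay ends at discharge or death, and ventilation duration is simply total days. A patient who dies early therefore gets a short value, just as a patient who recovers quickly does. WP2 and WP3 enrol invasively ventilated patients, and survival is itself a primary outcome there. If the treatment changes mortality, both durations would shift for that reason alone.

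**Working it through.** **Step 1: outcome type against named model**

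| ICU outcome | Type | Suits binary logistic regression? | Other model tied to it? |
|---|---|---|---|
| 28-day survival, need for ventilation (primary) | yes/no | yes | not needed |
| ICU and in-hospital mortality, complications | yes/no | yes | not needed |
| Length of stay | days | only if split | none |
| Ventilation duration | days | only if split | none |
| Ventilator-free days | days | only if split | none |

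As a check, a binary logistic model fitted to a simulated day count was rejected by the software, because the outcome must lie between 0 and 1. An ordinal (proportional-odds) logistic model ran on simulated ventilator-free days without a split. The article does not name that model.

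**Step 2: cost of a split, ventilator-free days**

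The article states that there is no sample size calculation, so there is no figure to reproduce. All inputs here are assumptions: 45% of controls at 0 days, the remaining 55% spread evenly over days 1 to 27, a common odds ratio of 1.5 (θ = ln 1.5 = 0.4055), and a two-sided 5% test.

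*Ordinal or rank analysis.* Power = Φ(θ·√[n(1 − Σp̄³)/6] − 1.96), where n is the number per group and p̄ is the average probability of each category over the two groups. Here 1 − Σp̄³ = 0.935. At n = 250, θ·√(250 × 0.935/6) = 2.531, so power = Φ(0.571) = 0.716.

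*Split.* Power = Φ(θ/SE − 1.96), with SE² = 1/(n·p₁q₁) + 1/(n·p₂q₂).
- Cut at >0 days: 0.550 against 0.647, SE = 0.1835, power = Φ(2.209 − 1.96) = 0.60.
- Cut at >14 days: 0.265 against 0.351, SE = 0.1952, power = Φ(2.077 − 1.96) = 0.55.

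| Per group | Ordinal/rank | Cut >0 | Cut >14 | Loss (points) |
|---|---|---|---|---|
| 150 | 50% | 40% | 36% | 10 to 14 |
| 250 | 72% | 60% | 55% | 12 to 17 |
| 500 | 95% | 88% | 84% | 7 to 11 |

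A simulation with 3,000 replicates gave 71.6%, 59.2% and 54.3% at 250 per group, and 50.8%, 41.1% and 37.1% at 150. These agree with the formulas.

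**Step 3: how far the loss depends on the assumptions**

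The same formulas at 250 per group:

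| Odds ratio | Controls at zero | Ordinal/rank | Cut >0 | Cut >14 |
|---|---|---|---|---|
| 1.5 | 30% | 74% | 51% | 59% |
| 1.5 | 60% | 67% | 61% | 47% |
| 1.25 | 45% | 28% | 23% | 20% |
| 2 | 45% | 99% | 96% | 95% |

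The less costly cut also changes: >14 is better with 30% at zero, and >0 is better with 45% or 60%.

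**Step 4: a duration outcome**

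Assume log-normal days with SD 0.7 on the log scale, 200 per group, and no allowance for death. Full-scale power is Φ(d/[0.7·√(2/200)] − 1.96) for a log-scale shift d. A median split compares 0.5 with Φ(d/0.7).
- d = 0.10: 30% against 21%.
- d = 0.15: 57% against 40%.
- d = 0.20: 82% against 62%.

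**Step 5: death**

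Take two hypothetical patients, one who dies on the ventilator on day 5 and one extubated alive on day 5. Both have a ventilation duration of 5. A linear, rank, count or split analysis of that number treats them alike, so this problem comes from the outcome definition and not from logistic regression.

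**The case against.** The strongest reply is that this is one loose sentence inside an option that may never be taken. The matched model is conditional, the whole paragraph is made subject to data structure, and the Abstract promises modelling suited to each data structure. Most listed outcomes are binary and suit logistic regression. The model for each secondary outcome is also commonly left to an analysis plan. All of this stands as a limit on scope. It does not remove the mismatch, because the sentence names one method without restriction and no other method is tied to the day counts.

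Several stronger readings are tempting, and the article does not support them.
- A reader might infer that logistic regression is fixed for every outcome in the study. The phrase is unqualified, but it sits in an optional analysis.
- A reader might infer that the analysis cannot be run without a split. That is true of binary logistic regression, which is the plain reading since the same term is used for day-28 survival and for the propensity model. An ordinal logistic model would need no split.
- A reader might infer that a cut-off will be picked with the data in hand. Data on 1500 patients had been collected by April 2023, but the article nowhere proposes to dichotomise.
- A reader might blame logistic regression for early death looking favourable. As Step 5 shows, that problem arises under any model that ignores death. For ventilator-free days, the added reference to being alive at day 28 suggests that survival is meant to be part of the outcome.

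**Conclusion.** The point holds in a limited form. If matching is done, the stated method does not fit three secondary outcomes in WP2 and WP3. No primary outcome, no binary secondary outcome and no WP1 outcome is affected. The handling of death in length of stay and ventilation duration is a related but separate weakness of definition.

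The mismatch rests on the text alone. Its cost rests on assumed inputs: roughly 7 to 17 points of power across 150 to 500 per group at an odds ratio of 1.5 with 45% at zero, and more or less than that under other inputs. The matched ICU numbers are not known, and the study sets no power target, so these figures illustrate the loss and do not estimate it. The sentence should be corrected, but this does not threaten the main conclusions of the study.

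**What to change.** 1. Limit the logistic regression sentence to binary outcomes: mortality, need for ventilation and complications.
2. Analyse ventilator-free days with a proportional-odds or rank-based method, with death as the worst category.
3. Analyse ventilation duration as time to extubation alive, and length of stay as time to discharge alive, each with death as a competing event. Say which discharge is meant, since the outcome is labelled as hospital stay but defined by ICU dates.
4. Use the same matched sets for these analyses as for the matched comparison of the binary outcomes.

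The cost is a few sentences in the analysis plan and standard software. No new variables are needed beyond the dates and vital status that the listed outcomes already require.

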## Abstract

**Background:**

In hospitalized patients with COVID-19, the dosing and timing of corticosteroids vary widely. Low-dose dexamethasone therapy reduces mortality in patients requiring respiratory support, but it remains unclear how to treat patients when this therapy fails. In critically ill patients, high-dose corticosteroids are often administered as salvage late in the disease course, whereas earlier administration may be more beneficial in preventing disease progression. Previous research has revealed that increased levels of various biomarkers are associated with mortality, and whole blood transcriptome sequencing has the ability to identify host factors predisposing to critical illness in patients with COVID-19.

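### Subphenotype heterogeneity is decided by one interaction P value on a ratio scale, which can mislead about absolute benefit in either direction when subphenotypes differ in baseline mortality

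*Protocol article*

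**What the plan says.** Methods, Statistical Analysis, states that clinical and biological data will be used to "perform latent class analysis to search for subphenotypes, which respond more favorably to corticosteroid treatment". The test is made by "including the latent class analysis-derived subphenotype, corticosteroid exposure, and an interaction term of the 2" "as c-variate in the above-described survival models". The decision rule follows: "Heterogeneity of treatment effect is considered to be present if the interaction term has a" P value below .05. No other criterion is given: no effect size, no interval and no absolute contrast by subphenotype.

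The same section describes the models that host the interaction:

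- One is firm and on the log-odds scale: "A multivariable logistic regression model will be used with high-dose corticosteroids as exposure and survival at day 28 as an outcome".
- One is optional and on the log-hazard scale: "A Cox proportional hazards model might be performed to determine the effect of high-dose corticosteroids on time to death".
- The rest are possibilities with no scale stated: "Other approaches involving censoring weights for differential loss to follow-up (eg, marginal structural models) or competing risks (eg, joint models) might be explored".

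The Abstract (Background) reports earlier findings that "increased levels of various biomarkers are associated with mortality". The article gives no mortality by subphenotype. It also does not say whether the derived subphenotype enters as an assigned class, as posterior probabilities or with a correction for classification error.

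**The concern.** An interaction in a logistic or Cox model asks whether the odds or hazard ratio differs between subphenotypes. The purpose set out in the Objective and the Introduction is a basis for personalised treatment, and the Introduction sets possible benefit against complications such as secondary infections. That weighing is done in absolute risk. Classes built from biological data are likely to differ in baseline mortality, because the article itself links such markers to mortality. When baseline risks differ, equal ratios imply unequal absolute benefits, and equal absolute benefits imply unequal ratios. A rule that looks only at the ratio-scale P value can therefore point the wrong way for the personalisation question.

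A second matter is conditional. Latent classes are estimated with error. If each patient's most likely class is entered as though observed, and the error does not depend on treatment or outcome given true class, the interaction is pulled towards zero and is easier to miss.

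**Working it through.** The article states no power, event count or class-specific risk for this analysis, so there is no figure to reproduce. Everything below rests on assumed inputs.

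**1. Common odds ratio, differing baseline risk.** Assumed: OR 0.70 for death; baseline 28-day mortality p of 10%, 20% or 50%. Modelling survival instead of death inverts the ORs and changes nothing else. Treated risk = OR × p/(1−p) ÷ [1 + OR × p/(1−p)].

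| Baseline risk | Treated risk | Reduction (points) |
|---|---|---|
| 10% | 7.2% | 2.8 |
| 20% | 14.9% | 5.1 |
| 50% | 41.2% | 8.8 |

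The log-OR interaction is exactly zero for every pair of rows, so the rule declares heterogeneity only at its 5% error rate, whatever the sample size. The absolute benefits differ 3.2-fold between 10% and 50% (8.8/2.8) and 1.7-fold between 20% and 50% (8.8/5.1).

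**2. Equal absolute benefit.** Assumed: a 5-point reduction everywhere. OR = [(p−0.05)/(1−p+0.05)] ÷ [p/(1−p)].

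- p = 10%: (0.05/0.95)/(0.10/0.90) = 0.47
- p = 30%: (0.25/0.75)/(0.30/0.70) = 0.78
- p = 50%: (0.45/0.55)/(0.50/0.50) = 0.82

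For 10% against 30%, the ratio of ORs is 0.778/0.474 = 1.64. Assume N = 1500 (the number collected by April 2023, used only as an illustration), half exposed, and 30% of patients in the higher-risk class. The cells then hold 525 patients per arm in the lower-risk class and 225 per arm in the higher-risk class. The standard error of the log ratio is √[1/(525×0.09) + 1/(525×0.0475) + 1/(225×0.21) + 1/(225×0.1875)] = 0.326. With ln 1.64 = 0.496, z = 1.52, and the rule declares heterogeneity in about 33% of studies. At N = 5000 it does so in about 79%.

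**3. What an additive test would do.** Take the common OR of 0.70 at 20% and 50% with the same cells, so that the gap in benefit is 8.8 − 5.1 = 3.7 points. Its standard error is √[0.2×0.8/525 + 0.149×0.851/525 + 0.5×0.5/225 + 0.412×0.588/225] = 5.2 points. Power is about 11% at N = 1500 and about a quarter at N = 5000. The 95% interval at N = 1500 is about ±10 points (1.96 × 5.2).

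**4. Class error, if assigned classes are used uncorrected.** Assumed: mortality 20% and 50%, class ORs 1.0 and 0.5 (true ratio 0.50), higher-risk class 30%, nondifferential error with equal sensitivity and specificity. Observed risks are mixtures weighted by the predictive values. At 90% accuracy:

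- Positive predictive value = 0.27/(0.27+0.07) = 0.794; negative predictive value = 0.63/(0.63+0.03) = 0.955.
- The higher-risk class shows 43.8% untreated and 30.6% treated; the lower-risk class shows 21.4% and 20.6%.
- Observed ratio of ORs = 0.59, and ln 0.591/ln 0.50 = 76% of the true interaction.

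At 95% and 80% accuracy, 87% and 55% are kept. Power at N = 1500 is 80% without class error, and 70%, 58% and 36% at 95%, 90% and 80% accuracy.

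The same can be indexed by the mean highest posterior probability, with two normal classes, 40% prevalence, control mortality 20% and 40%, and the same class ORs:

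| Mean highest posterior | Kept, modal assignment | Kept, pseudo-class draws (posterior without outcome) |
|---|---|---|
| 0.95 | 89% | 84% |
| 0.91 | 81% | 72% |
| 0.87 | 72% | 61% |
| 0.80 | 58% | 42% |

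Such pseudo-class draws attenuate more than modal assignment at every level.

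**The case against.** The strongest reply is that scale is a choice of estimand. A ratio-scale interaction is a conventional definition of effect modification and separates a different response from a merely different baseline risk. On an additive scale, a common OR would count as differential response only because one class is sicker. This stands. It is why the ratio interaction should stay and why the conclusion should not move wholly to risk differences. It does not rescue a rule that uses the ratio-scale P value alone when the stated purpose is personalised treatment.

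The other points are also partly right. The threefold contrast needs 10% against 50% mortality, and the article gives neither. The additive test has low power too, which favours reporting intervals over substituting another P value. If the relative effect also differs, the present rule can detect it. Marginal structural models could be fitted on an absolute scale, but they are only a possibility and no scale is attached to them.

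A reader might infer that the plan treats class as known and that its interaction is therefore shrunk. The article does not say so. Entering a derived subphenotype most plainly suggests an assigned class, but posterior weighting or a correction is not excluded, and a condensed article commonly leaves that detail to the full plan. Attenuation is a consequence under conditions and is not a stated fault.

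**Conclusion.** The point holds for the decision rule. A P value below .05 for a ratio-scale interaction is the only stated criterion for heterogeneity, and it can mislead about absolute benefit both ways. With assumed baseline mortality of 10% to 50%, a common OR of 0.70 spans 2.8 to 8.8 points unseen by the rule, while an equal 5-point benefit spans ORs of 0.47 to 0.82. That baseline risk differs between subphenotypes is plausible from the article but not shown in it, and the size depends entirely on that difference.

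The class-error point is secondary and conditional on uncorrected assigned classes and nondifferential error. Attenuation would then be roughly 10% at a mean highest posterior of 0.95 and 40% to 45% at 0.80, under assumed risks. The main treatment-effect analyses are unaffected; what is at stake is the conclusion about who responds better.

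**What to change.** - Keep the ratio-scale interaction. Report beside it the standardised day-28 risk difference in each subphenotype, and the difference between them, with confidence intervals.
- State that P of .05 or more will not by itself be read as absence of heterogeneity. No sample size is planned, so the interval should carry that message.
- State how class uncertainty is handled. If assigned classes enter the model, use a bias-adjusted three-step analysis (BCH or ML). Do not use pseudo-class draws from a posterior that omits the outcome, because they enlarge the bias.

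The cost is analysis work only; no new data are needed. Corrected intervals widen appreciably when classes separate poorly: if 58% of the interaction is kept, undoing this multiplies the estimate by about 1/0.58 = 1.7, and the interval grows broadly in proportion. The correction removes bias but does not restore lost power.

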**Methods:**

This is a retrospective, observational, multicenter study that includes adult patients who were hospitalized due to COVID-19 in the Netherlands. We will use the differences in therapeutic strategies between hospitals (per protocol high-dose corticosteroids or not) over time to determine whether high-dose corticosteroids have an effect on the following outcome measures: mechanical ventilation or high-flow nasal cannula therapy, in-hospital mortality, and 28-day survival. We will also explore biomarker profiles in serum and bronchoalveolar lavage fluid and use whole blood transcriptome analysis to determine factors that influence the relationship between high-dose corticosteroids and outcome. Existing databases that contain routinely collected electronic data during ward and intensive care admissions, as well as existing biobanks, will be used. We will apply longitudinal modeling appropriate for each data structure to answer the research questions at hand.

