#### Work Package 4: Biomarker Profiles and Whole Blood Genome Transcriptomes in High-Dose Corticosteroid Treatment

Work package 4a (WP4a) is used to investigate whether biomarker profiles in serum and BALF act as response predictors for high-dose corticosteroids on the outcome.

WP4b is used to investigate whether whole blood transcriptome analysis acts as a response predictor for high-dose corticosteroids on the outcome.

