Regarding WP4, patients are randomly selected and cases will be patients treated with high-dose corticosteroids, whereas controls will be patients who were not treated with high-dose corticosteroids. In WP4a, inverse probability treatment weighting and inverse probability of censoring weights will be used together in a marginal structural model. After we have analyzed the effect of high-dose corticosteroids on mortality and the other outcome measures, we will use this model to determine if the listed biomarkers modify the effect of high-dose corticosteroids on mortality.

In WP4b, we will identify transcriptome features that are differentially altered between cases and controls. Mean transcriptome levels will be compared using an unpaired *t*-test and *P* values will be adjusted for false-discovery rate using the Benjamini-Hochberg procedure. The log_2_ mean fold change of levels between cases and controls will also be calculated for each transcriptome. We will define transcriptome features as those with an adjusted *P* value of <.05 and a >2.0 or <–2.0 log_2_ mean fold change in level.

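### WP4b aims to find transcripts that predict response to high-dose corticosteroids, but its stated analysis compares expression by treatment received, with no outcome or interaction step

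*Protocol article*

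**What the plan says.** **Aim.** The Study Aims section, under Work Package 4, sets WP4b the task of testing whether "whole blood transcriptome analysis acts as a response predictor for high-dose corticosteroids on the outcome". The Methods part of the abstract says the study will "use whole blood transcriptome analysis to determine factors that influence the relationship between high-dose corticosteroids and outcome". The Primary Outcomes section adds that WP4 studies response on the same outcomes as the other work packages.

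**Analysis.** The Statistical Analysis section defines the WP4 groups by exposure: "cases will be patients treated with high-dose corticosteroids, whereas controls will be patients who were not treated with high-dose corticosteroids". For WP4b it then states that "we will identify transcriptome features that are differentially altered between cases and controls". The method is: "Mean transcriptome levels will be compared using an unpaired" t-test, Benjamini-Hochberg adjustment, and selection of transcripts with adjusted P below .05 and a log2 mean fold change above 2.0 or below -2.0. The description of WP4b ends there.

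**Neighbouring analysis.** For WP4a, the same section describes a marginal structural model with treatment and censoring weights, and then asks whether the listed biomarkers modify the effect of high-dose corticosteroids on mortality.

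**The concern.** A response predictor is an effect modifier: a transcript whose level changes the effect of treatment on outcome. Finding one requires treatment, expression and outcome in the same analysis. The WP4b method uses only treatment and expression. It therefore answers a different question, namely which transcripts differ between patients who did and did not receive high-dose corticosteroids.

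Two things are at stake. Transcripts that matter for response can be missed because they do not differ between the groups. Transcripts that are selected carry no evidence about response. WP4b is one of the two parts that support the personalised-treatment objective, so that objective would rest on an analysis that does not address it.

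**Working it through.** The article gives no sample size, power or effect size for WP4b, so there is no stated figure to reproduce. The check compares the question with the method, then works through what the stated rule can select.

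**1. Question and method side by side**

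| Element | Needed for the WP4b aim | Stated for WP4a | Stated for WP4b |
|---|---|---|---|
| Outcome | yes | yes (mortality and others) | no |
| Treatment | yes | yes | yes (defines the groups) |
| Marker | yes | yes (biomarkers) | yes (transcripts) |
| Effect-modification step | yes | yes | no |
| Adjustment for non-random treatment | yes | yes (weights) | no |

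**2. What the contrast estimates.** Write T for high-dose treatment, G for log2 expression and Y for outcome. The model that matches the aim is

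logit P(Y = 1) = a + bT + cG + d(T × G),

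and the question is whether d differs from 0. The WP4b test estimates

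Δ = E(G | T = 1) − E(G | T = 0).

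Δ contains neither Y nor d. If G is balanced between the groups, Δ = 0 whatever the value of d.

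**3. What happens to a balanced modifier under the full rule.** Assume, for illustration, an SD of 1 on the log2 scale and 50 patients per group; the article gives neither figure. The standard error of the observed difference is √(1/50 + 1/50) = 0.20. The cut-off of 2.0 therefore lies 2.0/0.20 = 10 standard errors from the expected value of 0. With 200 per group the standard error is √(1/200 + 1/200) = 0.10 and the distance is 20 standard errors. More patients make selection less likely.

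**4. What can produce a non-zero Δ.** The article names the sources itself. Study Design and Setting says regimens vary by wave, centre and patient, and that biobank material comes from Erasmus MC and Amsterdam UMC collections. The Discussion names bias by indication as a major issue. An unadjusted t-test carries all of these into Δ. Data Collection gives no sampling time relative to the start of high-dose treatment, so drug-induced expression is a further possible source. None of these implies d ≠ 0.

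**5. Whether another analysis fills the gap.** The effect-modification step in Statistical Analysis is given for WP4a and its listed biomarkers. The latent class interaction is described with the WP1 to WP3 models, tests a derived subphenotype, and does not name the transcriptome. Neither is a transcript-level response analysis for WP4b.

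**The case against.** **WP4b is exploratory and WP4 has outcomes.** The article calls this work exploration and a first step, WP1 to WP3 do not depend on it, and Primary Outcomes assigns outcomes to WP4 as a whole. This limits the reach of the problem but does not answer it. The WP4b method never brings those outcomes in, and no second step is stated in which they could enter. Nor is this detail left to an analysis plan: the article fixes the groups, test, multiplicity method and threshold.

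**Four stronger readings that a reader might infer are not supported.**

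- *WP4b could never surface a modifier.* Too absolute. A transcript that modifies the effect and also differs strongly between the groups could be selected. It would be selected for the difference, and the list could not separate it from the rest.
- *The log2 cut-off of 2.0 is a mistake for 2-fold.* It means 2² = 4-fold. It is symmetric and coherent on the log2 scale, and nothing in the article shows that 2-fold was intended or that the cut-off removes most candidates.
- *The rule would produce a long list of false markers.* This cannot be shown. With SD 1 and an assumed allocation log odds ratio of 0.8 per SD, with half the patients treated, the expected group difference is about 0.70, well below 2.0. On such inputs the rule would return little. Simulating a bare t-test at .05 would mislead, because it leaves out both the false-discovery correction and the cut-off.
- *The hits would be reported as treatment-selection markers.* The Discussion expects useful tools but also calls bedside translation highly challenging. No section says how WP4b hits will be reported.

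**The remedy has limits.** This stands. Pre-treatment samples may not exist in sufficient number, and transcriptome-wide interaction tests have low power.

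**Conclusion.** The point holds as a mismatch between aim and analysis. WP4b is meant to identify predictors of response on outcome, but its stated analysis tests association with treatment received, unadjusted, with no outcome or treatment-by-transcript step. For a modifier balanced between the groups the expected log2 fold change is exactly 0, so the rule would not select it at any realistic sample size.

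This follows from the form of the contrast. It does not depend on when blood was drawn or on how many patients are sampled; the SD and group sizes in the working serve only as illustration. How many non-modifying transcripts the rule would select cannot be determined from the article. The problem is confined to WP4b.

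**What to change.** **Preferred change.** In Statistical Analysis, replace the WP4b method with a model for each transcript of the outcome on high-dose exposure, expression and their interaction. Use the treatment and censoring weights planned for WP4a. Restrict it to samples drawn before high-dose treatment where they exist, and state the sampling time. Apply Benjamini-Hochberg to the interaction P values. Keep the treated-versus-untreated comparison as a descriptive analysis only.

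**Alternative.** If pre-treatment samples are too few, restate WP4b in Study Aims and in the abstract as a description of expression differences by treatment, and drop the response-predictor claim.

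**Cost.** The change needs new wording and analysis code, with no new samples. The usable number of patients falls where no pre-treatment sample exists. Power will be low. As an illustration, a single interaction test with 90% power at .05 has a standardised effect of 1.96 + 1.28 = 3.24. At .05/10,000 the critical value is 4.56 and power is Φ(3.24 − 4.56), about 9%. At .05/20,000 it is 4.71 and power is about 7%. The transcript counts are assumptions. Benjamini-Hochberg is less strict than this Bonferroni-type threshold, but close to it when true modifiers are few. The report should therefore say that the absence of interaction hits is weak evidence that no modifiers exist.
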